**Confidentiality Statement:**

## Synopsis

|                                                                                                                                                                                                                                                                                                                                                                                      |
|--------------------------------------------------------------------------------------------------------------------------------------------------------------------------------------------------------------------------------------------------------------------------------------------------------------------------------------------------------------------------------------|
| Purpose
The goal of the proposed study is to evaluate the feasibility and accessibility of pragmatic, remote, video-based pelvic floor muscle therapy (PFMT) for patients.                                                                                                                                                                                                 |
| Primary Objective
The primary objective of this study is to determine the feasibility of use of a video-based PFMT.                                                                                                                                                                                                                                                        |
| Secondary Objective
The secondary objective is to determine whether PFMT can improve quality of life (QoL) and reduce symptom burden.                                                                                                                                                                                                                                      |
| Study Design
Patients will complete a series of surveys before and after the intervention. They will complete 8 weeks of video-based PFMT with an initial and final in-person session with a pelvic floor therapist.                                                                                                                                                       |
| Study Date Range and Duration
December 2024 – August 2026                                                                                                                                                                                                                                                                                                                  |
| Number of Study Sites
Yale New Haven Hospital                                                                                                                                                                                                                                                                                                                              |
| Primary Outcome Variables
We will use direct patient evaluation by pelvic floor therapists, a validated system usability survey to evaluate the ease of use of the web-based platform containing PFMT videos and monitor for adverse events.                                                                                                                               |
| Secondary and Exploratory Outcome Variables (if applicable)
Short Form 12 score, Cleveland Clinic Incontinence Score (CCIS), Patient Assessment of Constipation Symptoms (PAC-SYM), International Consultation on Incontinence Questionnaire Short Form (ICIQ-SF), and Pelvic Organ Prolapse Symptom Score (POP-SS) to assess improvement in symptoms and quality of life. |
| Study Population
Study population will include patients who have an indication for referral for pelvic floor rehabilitation (PFR).                                                                                                                                                                                                                                         |
| Number of Participants                                                                                                                                                                                                                                                                                                                                                        |

We plan to enroll 10-20 patients. This is a pilot study aimed at assessing feasibility, so this sample size is similar to other feasibility trials.

**Study Schedule**

Patients will be expected to complete a 5–10-minute survey at initial enrollment. They will have one in-person session with a pelvic floor therapist prior to starting the 8-week video-based PFMT course. They will have a midpoint check in after 4 weeks to monitor progress. Afterwards, they will have a final in person session with a pelvic floor therapist along with a final set of surveys that should take an estimated 10-15 minutes. We have also attached a figure with the study design.

## Protocol Revision History

| Version Date | Summary of Substantial Changes |
|--------------|--------------------------------|
| 10/21/24     | First submission               |
| 12/11/24     | Second submission              |
| 3/7/25       | Third submission               |
| 3/11/25      | Fourth submission              |
| 3/13/25      | Fifth submission               |

## **Statement of Compliance**

This document is a protocol for a human research study. The purpose of this protocol is to ensure that this study is to be conducted according to the Common Rule at 45CFR46 (human subjects) and other applicable government regulations and Institutional research policies and procedures.

## Abbreviations

| Abbreviation | Explanation                 |
|--------------|-----------------------------|
| PFMT         | Pelvic floor muscle therapy |
| PFR          | Pelvic floor rehabilitation |
| QoL          | Quality of life             |
|              |                             |

## Glossary of Terms

| Glossary | Explanation |
|----------|-------------|
|----------|-------------|

# 1 Background/Literature Review

## 1.1 Background

Pelvic floor rehabilitation (PFR) is a group of therapeutic techniques used to help patients with pelvic floor dysfunction, such as urinary incontinence or fecal incontinence. The exercises commonly use in PFR include pelvic floor muscle therapy (PFMT) with biofeedback training, rectal balloon training or electrical stimulation. Together, these techniques aim to improve the strength, tone and endurance of the pelvic floor musculature and sphincter complex. For fecal incontinence, they have shown to decrease symptoms ranging between 50-80%. A meta-analysis looking at 18 trials utilizing PFMT for urinary incontinence found an improvement in symptoms in all studies.

Despite PFMT being shown to be efficacious for numerous different pelvic floor dysfunction disorders, less than 50% of patients referred are compliant with the recommend duration of treatment. Previous studies found that inconvenience, cost, lack of knowledge and discomfort around the concept of PFMT are all reasons why patients may have poor compliance. Patients have shown a positive reception to telehealth-based PFMT visits. It is not known if a hybrid approach to PFMT including both in-person and video-based training videos may help to alleviate some of these barriers while providing the same adequate amount of guidance, improvement in symptoms and QoL for patients. Thus, the purpose of this study is to evaluate the feasibility and acceptability of a web-accessible 8-week video-based PFMT for pelvic floor disorders.

## 1.2 Prior Experience (if applicable)

Our group conducted a study on patient reported barriers to completion of in-person PFR. We found the average time between referral and attendance of the first PFR session was 10 weeks. The two major barriers to completion included delay in available sessions (24%) and travel distance for attendance (20%). Furthermore, 35% of patients stated they would be amenable to a hybrid option using either telehealth or video-based strategies and 58% of patients would attend more sessions if there was a video-based option.

# 2 Rationale/Significance

## 2.1 Rationale and Study Significance

PFMT is a non-invasive tool to improve symptoms of pelvic floor dysfunction, but there are many barriers for patients to successfully attend and complete the trainings, with the most common reasons cited in a retrospective study conducted by our group including delay in available sessions and travel distance for attendance. It is not known if these exercises could be adequately learned through a video-based training module that would give patients back privacy and time.

## 2.2 Purpose of Study/Potential Impact

Evaluating the feasibility and safety of video-based PFMT will allow us to determine if this video-based training could be offered as a treatment alternative for patients with pelvic floor dysfunction.

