## 4.2 Outcome Variables

### 4.2.1 Primary Outcome Variables

SUS, percentage of video completion, change in the graded evaluation of exercises by pelvic floor therapist pre and post intervention, adverse events

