### 4.3.1 Number of Participants

A total of 10-20 patients will be enrolled in the study.

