#### 5.1.1 Data Collection

The survey information will be collected by a trained survey either in person or filled out independently by the study participant using a Yale-licensed Qualtrics platform. If there are technical difficulties, a paper-based version of the assessment tool will be substituted and later inputted. This data and the clinical data will be collected from the electronic medical records (e.g., Epic® chart reviews) and will be securely stored in the HIPAA compliant RedCap database. The assessment by the pelvic floor therapist will also be secured inputted into the RedCap database.

At the completion of the study period, we will compare the assessment of PFMT adequacy as assessed by the pelvic floor therapists, usability of the video-based application, and any adverse events as our primary outcome for feasibility and safety. We will analyze the change in the SF-12 score, CCIS, PAC-SYM, pre and post intervention to evaluate any change as our secondary outcome evaluating for efficacy of video-based PFMT.

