#### 5.1.2 Adverse Events Definition and Reporting

All patients will be provided with the contact information of the Principal Investigator if they feel that they have been adversely affected by participating in the surveys or in the in-person or video-based PFMT sessions.

This protocol presents minimal risks to the subjects and Unanticipated Problems Involving Risks to Subjects or Others (UPIRSOs), including adverse events, are not anticipated. In the unlikely event that such events occur, Reportable Events (which are events that are serious or life-threatening and unanticipated (or anticipated but occurring with a greater frequency than expected) and possibly, probably, or definitely related) or Unanticipated Problems Involving Risks to Subjects or Others that may require a temporary or permanent interruption of study activities will be reported immediately (if possible), followed by a written report within 5 calendar days of the Principal Investigator becoming aware of the event to the IRB (using the appropriate forms from the website) and any appropriate funding and regulatory agencies. The investigator will apprise fellow investigators and study personnel of all UPIRSOs and adverse events that occur during the conduct of this research project through weekly lab meetings to survey the progress of the study. The protocol's research monitor(s), e.g., Data and Safety Monitoring Boards, study sponsors, funding and regulatory agencies, and regulatory and decision-making bodies will be informed of physical harm adverse events within 5 days of the event becoming known to the principal investigator.

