### 5.4.2 Sample Size Considerations

This is a feasibility study with no prior literature publishing on the use of video-based PFMT. Based on prior feasibility studies, the sample size will be between 10-20 patients.

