### 5.4.3 Planned Analyses

The primary analysis to evaluate for feasibility and safety will involve the percentage of patients who successfully learned PFMT, analysis of incidence of adverse events and overall score of usability for the web-based videos. We will also evaluate the ability of participants to successfully complete the exercises based on the graded scoring by the pelvic floor therapists. Analysis of secondary outcomes

related to symptom improvement and quality of life will analyze SF-12, CCIS, PAC-SYM, ICIQ-SF and POP-SS scores.

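### Section 2.2 promises a determination on offering the videos, but one group of 10–20 patients cannot support its safety part

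*Protocol*

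**What the plan says.** The purpose statement in Protocol Section 2.2 reads: "Evaluating the feasibility and safety of video-based PFMT will allow us to determine if this video-based training could be offered as a treatment alternative". Feasibility and safety are named together as the basis of that determination.

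Safety enters the primary results in three places. Section 4.2.1 ends its list of primary outcomes with "change in the graded evaluation of exercises by pelvic floor therapist pre and post intervention, adverse events". Section 5.1.1 counts "any adverse events as our primary outcome for feasibility and safety". Section 5.4.3 says: "The primary analysis to evaluate for feasibility and safety will involve the percentage of patients who successfully learned PFMT, analysis of incidence of adverse events". The primary objective in Section 3.2 names only feasibility and accessibility, so safety is primary through the outcomes and the analysis, not through the objective.

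On size, Section 4.3.1 says "A total of 10-20 patients will be enrolled in the study", and Section 5.4.2 gives the reason: "Based on prior feasibility studies, the sample size will be between 10-20 patients". There is no control group. The protocol gives no expected event rate, acceptable event rate or safety criterion.

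Two further passages bear on the event count. Section 5.1.2 says: "This protocol presents minimal risks to the subjects and Unanticipated Problems Involving Risks to Subjects or Others (UPIRSOs), including adverse events, are not anticipated". Section 5.4.6 removes from the study patients who complete under 75% of the videos or who miss the first or last in-person visit.

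**The concern.** Section 2.2 gives the study a property, the ability to determine something, and safety is half of what that determination rests on. For safety, the protocol names one input: the incidence of adverse events in 10–20 people. Section 2.3.1 accepts that patients exercising unsupervised at home could hurt themselves, and that they give up standard visits to take part, so the safety question is a real one.

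A low or zero count is a plausible result. In a group this small it is compatible with a per-patient risk that few would call established safety. If the conclusion is drawn as Section 2.2 phrases it, a primary statement about safety could carry more weight than the data can bear, and it would feed directly into whether the videos are offered.

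**Working it through.** The protocol has no calculated figure to reproduce: the sample size is set by precedent. The check is how tightly 10–20 patients can bound a per-patient adverse-event risk.

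**Inputs**
- n = 10 and 20, the ends of the range in Section 4.3.1, with 15 as a midpoint.
- Confidence level: an assumption, since the protocol gives none. One-sided 95% is the main case, and two-sided 95% shows the range.
- Events observed: 0 or 1.

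**Zero events.** The exact (Clopper-Pearson) upper limit p solves (1 − p)^n = α, so p = 1 − α^(1/n), with α = 0.05 one-sided or 0.025 two-sided.

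| n | one-sided 95% | two-sided 95% |
|---|---|---|
| 10 | 1 − 0.05^(1/10) = 25.9% | 1 − 0.025^(1/10) = 30.8% |
| 15 | 1 − 0.05^(1/15) = 18.1% | 1 − 0.025^(1/15) = 21.8% |
| 20 | 1 − 0.05^(1/20) = 13.9% | 1 − 0.025^(1/20) = 16.8% |

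**One event.** The limit solves (1 − p)^n + n·p·(1 − p)^(n−1) = α, which is the 1 − α quantile of Beta(2, n − 1).
- One-sided 95%: 39.4% at n=10 and 21.6% at n=20.
- Two-sided 95%: 44.5% at n=10 and 24.9% at n=20.

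**Chance of seeing no event.** This is (1 − p)^n. The true risks are assumptions, because the protocol states none.
- True risk 5%: 0.95^10 = 59.9% at n=10; 0.95^20 = 35.8% at n=20.
- True risk 10%: 0.90^10 = 34.9% at n=10; 0.90^20 = 12.2% at n=20.

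**Effect of the Section 5.4.6 exclusions.** Suppose one patient in five is removed (an assumption). Then 8 of 10 or 16 of 20 remain, and the zero-event one-sided limits become 1 − 0.05^(1/8) = 31.2% and 1 − 0.05^(1/16) = 17.1%. The exclusions could also remove someone who stopped because of harm, which would lower the observed incidence as well as the denominator.

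**The case against.** The strongest reply is that the protocol never makes the mistake it might be charged with. Several stronger readings are tempting, and the document does not support them.

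- **That few or no events will be read as safe.** No passage says so. There is no safety threshold or decision rule, and neither hypothesis in Section 3.1 mentions safety. This objection stands in full. What remains is that Section 2.2 promises a determination and nothing elsewhere limits it.
- **That Section 2.2 rests on safety alone.** It names feasibility as well, and Section 5.4.3 also brings in learning of the exercises and usability. The concern therefore covers only the safety part.
- **That the missing confidence limit is itself the error.** An interval may well be specified in a statistical analysis plan that is not at hand, so its absence from the protocol is not a finding. But no interval makes 10–20 patients sufficient for the determination in Section 2.2.
- **That risks of 14–26% go unexcluded throughout.** The two figures are zero-event limits at different sample sizes. With 0 of 20, risks above 13.9% are excluded at the one-sided 95% level; a true risk of 20% would give no events with probability 0.8^20, about 1%.
- **That Section 5.1.2 forecasts zero events.** Its sentence concerns unanticipated problems and sits in a paragraph on reportable events, while Section 2.3.1 lists discomfort and worsening as possible. It is not a forecast of total adverse-event incidence.

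It is also fair to say that the synopsis presents this as a pilot, that Section 2.2 says only that the videos could be offered, and that any pilot of this size bounds harm loosely. The size is legitimate for a pilot. The difficulty is the verb in Section 2.2, which claims more than a pilot delivers.

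**Conclusion.** The concern holds in a limited form. The safety part of the determination in Section 2.2 is beyond a single group of 10–20 patients. Even the most favourable result, no events, leaves a one-sided 95% upper limit between 13.9% (n=20) and 25.9% (n=10), or 16.8% to 30.8% two-sided. One event raises the one-sided limits to 21.6% and 39.4%.

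The limits treat patients as independent and count each patient once. The confidence level is assumed, but neither level shown changes the conclusion. The 5% and 10% risk scenarios and the 20% loss are illustrations; the conclusion does not depend on them. The study can run as designed. What should change is the stated inference and the basis of the primary safety statement.

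**What to change.** - **Section 2.2:** say that the study gives preliminary safety information that can inform, but not determine, whether the videos could be offered as an alternative.
- **Section 5.4.3:** report the number of patients with at least one adverse event, with an exact (Clopper-Pearson) upper confidence limit at a stated level. Base the safety statement on that limit, not on the observed percentage or on the absence of events.
- **Denominator for that result:** all patients who started the videos, not only those kept after the Section 5.4.6 exclusions. Section 5.4.6 should say that its exclusions do not apply to the safety count.

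The cost is a change of wording in these sections and one exact interval. No extra patients or procedures are needed. The downside is a less favourable safety claim.

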## 2.3 Potential Risks and Benefits

### 2.3.1 Potential Risks

#### Pelvic Floor Muscle Therapy Sessions (in-person):

Participating in PFMT can be time consuming and may be uncomfortable for some patients. There is no guarantee that the instruction and exercises in these sessions will prevent patients from having persistent or worsening pelvic floor dysfunction. A trained physical therapist will be supervising and teaching these sessions. Patients can opt out of certain exercises if desired.

**Pelvic Floor Muscle Therapy Sessions (video-based):**

Practicing PFMT using the video-based application may similarly be time consuming and uncomfortable for patients to perform. Additionally, as patients will be performing these exercises alone without supervision, there is the risk of harm to self. There is no guarantee that the instruction and exercises in these sessions will prevent patients from having persistent or worsening pelvic floor dysfunction as they are opting out of standard of care visits. Patients can choose to opt out of certain exercises if desired.

**Surveys:**

The surveys administered may be tiring and/or sensitive for patients. All patients will be informed that any questions they do not feel comfortable answering are optional. The surveys used to evaluate for fecal incontinence, constipation and QoL are all validated questionnaires from pre-existing literature. The survey used to evaluate the efficacy of the video-based PFMT is also validated and should not incur any harm to patients.

**Medical Record Review:**

The medical record of each patient will be reviewed by the study staff to extract demographic information. The risk of breach of confidentiality will be minimized with adherence to the Yale New Haven Health Data Security rules. The questionnaire and outcomes data will be stored on HIPAA compliant RedCap database.

We do not anticipate any long-range risks.

**2.3.2 Potential Benefits**

**Short term:** Patients may have improvement in pelvic floor dysfunction and QoL

**Long term:** Patients may have improvement in pelvic floor dysfunction and QoL. If successful, the videos could be developed into a mobile based application and offered as an alternative treatment method.

## 3 Study Purpose and Objectives

**3.1 Hypothesis**

**Hypothesis A:** Video-based PFMT can be easily followed and used to practice PFMT

**Hypothesis B:** Video-based PFMT will help to reduce symptoms of pelvic floor disorders and improve the QoL of participants

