**3.3 Secondary Objective (if applicable)**

To determine whether video-based PFMT can improve symptomatology and QoL.

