## 4 Study Design

### 4.1.1 General Design Description

Patients will be enrolled during the clinic visit when they are initially referred for PFR. It will be explained that they are forgoing standard of care of all in-person pelvic floor rehabilitation and will complete the initial survey at this time. They will then have an introductory session with a pelvic floor therapist to assess their baseline function, which does not differ from the standard of care other than the pelvic floor therapist using a graded scoring system to assess exercise completion ability. This initial visit will be prioritized as the waitlist for pelvic floor rehabilitation can be up to 6 months. Then they will complete the 8 weeks of remote, self-directed video-based PFMT. At the midway point after completing 4 weeks of the remote, self-directed video based PFMT, patients will be contacted by a member of the research team to elicit feedback and complete a system usability scale to evaluate patient perspective of the online training program. After this period, they will have another in-person session with the same pelvic floor physical therapist to assess ability to complete exercises successfully with the same graded scoring system. They will then complete a system usability scale survey and repeat the initial surveys for QoL and symptom surveys within 2 weeks of the final in person pelvic floor therapist appointment.

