### 4.3.2 Eligibility Criteria/Vulnerable Populations

Eligibility will be assessed by a member of the study team reviewing outpatient clinic visits to colorectal surgery and urogynecology clinics at Yale New Haven Hospital and its associated ancillary clinic sites.

In order to be eligible for inclusion in this study, an individual must meet all of the following criteria:

1. Diagnosis of one of the five following diagnoses with referral for PFR
  - a. Urinary incontinence
  - b. Pelvic pain
  - c. Fecal incontinence
  - d. Postpartum-related symptoms
  - e. Constipation
2. 18 years or older
3. English-speaking
4. Access to internet

Vulnerable populations: none

Exclusion criteria:

1. Unable to access web-based videos
2. Unable to speak English

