## 5.4 Statistical Method

### 5.4.1 Statistical Design

Demographic information will be reported using descriptive statistics. Categorical variables will be analyzed with chi-squared test and continuous variables will be analyzed with Wilcoxon Rank sum test. Paired T-test will be used to evaluate differences pre and post treatment of the following measures:

- 1) amount of supervision and cues needed by the pelvic floor therapist
- 2) difference in graded scoring of exercises by the pelvic floor therapist
- 3) CCIS scores
- 4) PAC-SYM score
- 5) SF-12 Scores
- 6) ICIQ-SF Scores
- 7) POP-SS Scores

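### The secondary aim is worded as efficacy, but a single-arm paired t-test can only show change from baseline (minor)

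*Protocol*

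**What the plan says.** Three places in the protocol attribute benefit to the programme:

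- Section 3.1, Hypothesis B: "Video-based PFMT will help to reduce symptoms of pelvic floor disorders and improve the QoL of participants".
- Section 3.3, secondary objective: "To determine whether video-based PFMT can improve symptomatology and QoL".
- Section 5.1.1: scores are compared "pre and post intervention to evaluate any change as our secondary outcome evaluating for efficacy of video-based PFMT".

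The design is a single group. Section 4.1.1 gives every participant the same course ("Then they will complete the 8 weeks of remote, self-directed video-based PFMT") and names no comparator. The baseline survey is completed at the clinic visit where the patient is first referred. An in-person therapist session, the video course and a second in-person session follow, and then the final surveys.

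Section 5.4.1 gives the analysis: "Paired T-test will be used to evaluate differences pre and post treatment of the following measures". Five of the seven listed measures are symptom or quality-of-life scores. Section 5.4.2 sets the size: "Based on prior feasibility studies, the sample size will be between 10-20 patients". Under sections 4.2.2 and 5.3.3 every patient completes the SF-12 but only one of the four symptom instruments.

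No section limits causal interpretation of the secondary results or gives an expected change without treatment.

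**The concern.** The paired t-test asks whether the mean within-patient change differs from zero. That is not the question in Hypothesis B or section 3.3, which is whether the programme causes improvement. The two questions coincide only if scores would have stayed still without the videos, and nothing in the protocol supports that. Three other sources of change are built into the design:

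- **Regression to the mean.** Patients enter, and baseline is recorded, at the visit where their symptoms led to referral.
- **Natural course.** Symptoms may change over the weeks between surveys whatever the patient does. One of the five eligible diagnoses is "Postpartum-related symptoms", for which change over time is plausible, although the protocol does not quantify it.
- **The in-person sessions.** Both therapist visits fall between the baseline and final surveys, so even a real benefit could not be credited to the videos alone.

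At stake is what the trial may conclude. As worded, a significant p-value answers the secondary objective with a yes that the design cannot support.

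**Working it through.** **The plan's own figure.** There is nothing to reproduce. The sample size of 10-20 rests on precedent from other feasibility studies, with no effect size, SD, power or significance level. I assume a two-sided 5% level, so the nominal chance of a significant result in the direction of improvement is 2.5% when the true mean change is zero.

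**Inputs**

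- n = 10 to 20 for the SF-12 (sections 5.4.2 and 5.3.3).
- n of about 3 to 5 per symptom scale. This assumes an even split over four instruments: 10/4 = 2.5 and 20/4 = 5.
- b, how far the mean baseline lies on the worse side of the patients' long-run mean, in SD units: 0.5 or 1 (assumption).
- r, test-retest correlation: 0.6 or 0.8 (assumption).
- True effect of the programme: zero.

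**Formulas**

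- Expected improvement from regression to the mean = (1 - r) × b.
- SD of change = √(2(1 - r)).
- Standardised drift dz = (1 - r)b / √(2(1 - r)).
- Chance of significant improvement = P(T > t with 0.975 and n - 1 df), where T is noncentral t with n - 1 df and noncentrality dz√n.

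**Results with an inert programme**

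| b | r | Expected improvement (SD) | SD of change | dz | n=3 | n=5 | n=10 | n=20 |
|---|---|---|---|---|---|---|---|---|
| 0.5 | 0.8 | 0.10 | 0.63 | 0.16 | 3.8% | 4.7% | 6.5% | 9.9% |
| 0.5 | 0.6 | 0.20 | 0.89 | 0.22 | 4.4% | 5.9% | 9.3% | 15.6% |
| 1 | 0.8 | 0.20 | 0.63 | 0.32 | 5.4% | 8.0% | 14.4% | 26.9% |
| 1 | 0.6 | 0.40 | 0.89 | 0.45 | 7.1% | 12.0% | 24.4% | 47.6% |

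The n=10 and n=20 columns apply to the SF-12 (about 7-24% and 10-48%). The n=3 and n=5 columns apply to each symptom scale (about 4-12%). With b = 0 every entry is 2.5%.

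**Precision.** The 95% CI half-width, in SDs of change, is t(0.975, n - 1)/√n:

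- n=5: 2.776/√5 = 1.24
- n=10: 2.262/√10 = 0.72
- n=20: 2.093/√20 = 0.47

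At five patients per symptom scale, an observed mean change of one full SD of change would still have an interval that includes zero.

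**The case against.** The case for leaving the text alone has several parts.

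**The false-improvement rates come from an assumption.** This is correct. Eligibility in section 4.3.2 requires a diagnosis and referral but sets no symptom-score threshold, which is the usual driver of strong regression to the mean. A reader might infer that an inert programme would often look beneficial. The documents do not support that: the rate runs from 2.5% with no drift to 48% in the least favourable scenario above, and nothing in the protocol locates the trial within that range. What stands is that it can happen.

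**The SF-12 sample size does not carry over to the symptom scales.** Also correct. Each patient completes one of four, so for the symptom half of Hypothesis B false improvement is uncommon under an even split and imprecision is the larger limit. An uneven split would raise the rate for the commonest scale.

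**The trial is about feasibility.** Sections 3.2 and 5.4.2 say so, and section 2.2 ties the decision on offering the videos as an alternative to feasibility and safety. A reader might infer that a significant secondary result would be used to establish the videos as an effective substitute for in-person care, but the protocol does not state that use. This limits severity. It does not remove the conflict, because section 3.3 is itself an objective and section 5.1.1 names efficacy.

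**A hypothesis is only an expectation, and the paired t-test is valid for within-patient change.** Both are true. Section 5.4.1 on its own claims no more than a pre-post difference. The fault is in the link made in sections 3.3 and 5.1.1 from that difference to efficacy.

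**Reporting detail belongs in the SAP.** Partly accepted: the format of tables can wait. What the secondary analysis is meant to conclude is fixed in the protocol's objectives and should be corrected there.

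**Conclusion.** The point holds in a limited form. Sections 3.1 (Hypothesis B), 3.3 and 5.1.1 promise a conclusion about treatment effect that one arm and a test of zero mean change cannot give, and no other section qualifies it. That conflict rests on the text alone and needs no assumption.

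The numerical size does rest on assumptions: baseline 0.5 to 1 SD worse than the long-run mean, test-retest correlation 0.6 to 0.8, a two-sided 5% level, and an even split over the symptom scales. The calculation covers regression to the mean only; natural course and the therapist sessions are not quantified.

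A reader might also infer that the design is deficient for want of a control arm. That does not follow. An uncontrolled pilot suits the feasibility aim, and only the claim attached to the secondary scores exceeds it. Severity: minor.

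**What to change.** - **Section 3.1, Hypothesis B, and section 3.3:** reword so that the aim is to describe within-patient change from baseline in symptom scores and quality of life.
- **Section 5.1.1:** delete the description of the change as a "secondary outcome evaluating for efficacy of video-based PFMT" and call it change from baseline.
- **Sections 5.4.1 and 5.4.3:** present the secondary analysis as estimated mean change with a 95% confidence interval for each instrument, and state that no treatment effect is inferred from it.

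No control arm, extra patients or extra data are needed, and the feasibility objective is untouched. The cost is a protocol amendment to wording, which section 6.10 requires the IRB to approve before it takes effect. The drawback for the investigators is a less favourable secondary claim.
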